### Study population

This study will enroll a total of 200 patients with septic shock and elevated HR (≥ 95 bpm) despite a hemodynamic optimization phase of at least 24 h but a maximum of 36 h in which they received adequate fluid resuscitation and continuous vasopressor treatment (according to the Surviving Sepsis Campaign Guidelines 2016 [40]). Detailed inclusion and exclusion criteria are displayed in Table 2.

**Table 2 Tab2:** Inclusion/exclusion criteria

Inclusion criteria 1. Informed consent 2. Age ≥ 18 years 3. Confirmed septic shock: a. Confirmed or suspected infection b. Acute increase of ≥ 2 points on SOFA Score c. Need for continuous vasopressor therapy to maintain a mean arterial pressure (MAP) of > 65 mmHg despite adequate fluid resuscitation d. Blood lactate > 2 mmol/L (18 mg/dL)^a^ 4. Tachycardia and/or tachyarrhythmia with heart rate ≥ 95 bpm 5. Norepinephrine infusion rate ≥ 0.2 μg/kg/min at the time of study inclusion 6. Patients must have undergone a hemodynamic optimization period of at least 24 h but a maximum of 36 h, during which period they received continuous vasopressor treatment and standard treatment for septic shock according to the SSCG 2016 guidelines ^a^Presence of blood lactate > 2 mmol/L (18 mg/dL) and increase of ≥ 2 points on SOFA score are mandatory for the diagnosis of septic shock, but must not necessarily be present at the time of study inclusion Exclusion criteria: 1. Any form of compensatory tachycardia 2. β-blocker treatment within 72 h before randomization 3. Sick sinus syndrome, or second or third degree AV block 4. Patients with any form of cardiac pacing 5. A known serious cardiovascular condition such as ischemic stroke or transient ischemic attack within the last six months, or pre-existing heart failure NYHA class III or IV 6. Cardiogenic shock 7. MAP < 65 mmHg 8. Known pulmonary hypertension 9. Known terminal illness other than septic shock with expected patient’s survival < 28 days 10. Known presence of an advanced condition to withhold life-sustaining treatment 11. Patients for whom a “Do Not Resuscitate” (DNR) order exists 12. Known sensitivity to any component of the study medication (e.g. landiolol, mannitol) 13. Participation in a clinical drug trial within 30 days before randomization 14. Any condition that, in the investigator’s opinion, makes the individual unsuitable for study participation (to be documented) 15. Pregnant or breast-feeding patients 16. Untreated pheochromocytoma	

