### Randomization, blinding, and treatment allocation

Patients fulfilling the selection criteria are randomized in a 1:1 ratio to one of the two groups (landiolol or control) after informed consent, as required by local law, has been obtained. The presence of atrial fibrillation in the hemodynamic optimization period is used as a stratification factor for randomization. As this is an open label study, investigators and other study personnel will not be blinded to the treatment.

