### Endpoints

The primary efficacy endpoint is HR response (HR = 80–94 bpm) and maintenance thereof without increase in vasopressor requirements during the first 24 h after treatment start.

Secondary efficacy endpoints will consist of ICU and 28-day mortality, ICU and hospital stay duration, SOFA score, and inotrope and vasopressor support requirements. Efficacy and safety endpoints are listed in Table 3.

**Table 3 Tab3:** Efficacy and safety endpoints

Primary endpoint: • HR response (i.e. HR = 80–94 bpm) and maintenance thereof and no increase in vasopressor requirements during the first 24 h after treatment start Secondary endpoints: • Change in vasopressor requirements over the study period (dose and duration) • HR response (i.e. HR = 80–94 bpm) during the first 24 h after treatment start • 28-day mortality (all cause) • ICU mortality (all cause) • Duration of ICU stay (survivors/non-survivors) • Duration of hospital stay (survivors/non-survivors) • SOFA score (as long as the patient is treated with vasopressors) on days 1, 2, 3, 4, 7, 10, 13, 16, 19, 22, 25, and 28 • Daily inotropic requirements (as long as the patient is treated with vasopressors) Safety endpoints: • Incidence rate of bradycardic episodes requiring intervention • Incidence of adverse events (AE) • Incidence of serious adverse events (SAE)	

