### Statistical analysis

The hypothesis that Group L is superior to Group C in proportion of patients who reached the primary endpoint will be demonstrated if the lower limit of the two-sided 95% Newcombe confidence interval of difference pL-pC is above zero, where pL and pC are percentages of patients who reached the primary endpoint in Group L and Group C, respectively. *P* values based on Cochran–Mantel–Haenszel (according to SAS® terminology) will be presented together with the confidence intervals to evaluate statistical significance of association between treatment group and outcome after adjustment for the stratification group. For the purpose of exploratory analysis, the individual criteria of the primary endpoint, heart rate response (i.e. HR = 80–94 bpm) reached (also defined as secondary endpoint), heart rate response reached and maintained and no increase in vasopressor requirements during the first 24 h, will be compared separately between treatment groups. Additional subgroup and sensitivity analyses will have exploratory character and will be defined in all details in the SAP.

Secondary endpoints with continuous, ordinal, and binary variables measured at multiple time-points will be analyzed as longitudinal data by linear, ordinal logistic, logistic, or log-binomial regression models with repeated measures. Covariates used in the models will be (but not limited to) treatment, visit, stratification group, and interaction treatment/visit. For continuous variables baseline value of the outcome variable will be a covariate as well. Distribution of data and a feasibility check of planned analyses will be performed before finalization of SAP and alternative statistical methods will be defined if assumptions on the application of the planned methods are not met (e.g. ln-transformation of data, non-parametric method, or other alternative way). ICU mortality and 28-day mortality will be analyzed using the same methods as for the primary endpoint. Duration of ICU stay and duration of hospital stay (in survivors/non-survivors) will be analyzed as time-to-event data (using Kaplan–Meier curve and using log-rank test or Wilcoxon test and/or proportional hazards regression model if appropriate).

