For secondary analyses, no multiplicity adjustment is planned; therefore, a higher rate of type-I error must be considered in interpretation of results of secondary analyses. The analysis of secondary endpoints/analyses can provide supportive evidence related to the primary objective, but no confirmatory conclusion based on secondary analyses can be done.

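### ICU and hospital stay are to be compared between arms within survivors and within non-survivors, which are not randomised comparisons; the comparison should be made in all randomised patients with death as a competing event

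*Protocol article*

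**What the plan says.** The endpoint table (Endpoints, Table 3) lists two length-of-stay endpoints, each already split by survival status: "Duration of ICU stay (survivors/non-survivors") and "Duration of hospital stay (survivors/non-survivors"). The Statistical analysis section repeats the split: "Duration of ICU stay and duration of hospital stay (in survivors/non-survivors) will be analyzed as time-to-event data". It then attaches between-arm tests to that split, naming the methods as follows: "using Kaplan–Meier curve and using log-rank test or Wilcoxon test and/or proportional hazards regression model if appropriate".

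The same section treats survival as an outcome in its own right: "ICU mortality and 28-day mortality will be analyzed using the same methods as for the primary endpoint". It closes with a caution on all secondary analyses: "no confirmatory conclusion based on secondary analyses can be done".

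The article states no comparison of stay in all randomised patients, no handling of death as a competing event, and no endpoint that combines stay with survival.

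**The concern.** Randomisation makes the two arms comparable as a whole. It does not make survivors on landiolol comparable with survivors on control, because treatment may affect who survives. If landiolol keeps alive some patients who would have died on control, and those patients need a long stay, the landiolol survivors will on average stay longer although no patient's stay was prolonged. If landiolol causes early deaths among the sickest, its survivors' stay will look shorter.

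The two subsets also read in opposite directions. Among survivors, a shorter stay is an earlier recovery. Among patients who die in the unit, stay is the time to death, so shorter is not a gain. Neither test answers the question a clinician would ask, which is whether patients leave the ICU or hospital alive sooner. What is at stake is the reading of two secondary endpoints, not the primary result.

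**Working it through.** **The plan's own figures.** The article gives no mortality or stay figure, so there is nothing on this point to reproduce. The arm size comes from the sample size of 200 and 1:1 randomisation, hence 100 per arm. That size agrees with the stated basis (60% against 40%, 80% power; two-sided 0.05 taken, in line with the two-sided 95% interval): n = [1.960·√(2·0.5·0.5) + 0.842·√(0.6·0.4 + 0.4·0.6)]² / 0.2² = 96.9, so 97 per arm, and 100 per arm gives 81.2% power. Every input below is an assumption.

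**No effect on survival.** With 40% mortality in both arms and the same case mix, 4,000 simulated trials of 100 per arm gave about 5% total rejection in each subset. The split then does no harm to the error rate.

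**Moderate selection.** A severity score u ~ N(0, 1) drives both outcomes: logit P(death) = −0.45 + u + log(0.5) on landiolol, and log stay = log 12 + 0.35u + N(0, SD 0.5). Treatment changes no patient's stay.

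| | Control | Landiolol |
|---|---|---|
| Mortality | 41% | 28% |
| Median stay, survivors (days) | 10.7 | 11.1 |
| Median stay, non-survivors (days) | 14.2 | 14.9 |

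Both differences are selection alone. Over 20,000 simulated trials with 100 per arm and a two-sided 0.05 log-rank test, the survivor test found landiolol significantly longer in 5.5% of trials and shorter in 1.1% (nominal 2.5% each). The non-survivor test found it longer in 4.0% and shorter in 1.7%.

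**Stronger selection.** Three kinds of patient are assumed, with gamma-distributed stay (shape 2): those who survive in either arm (mean 15 days), those who die in either arm (mean 7 days), and those saved by landiolol, who die at a mean of 12 days on control and stay a mean of 25 or 30 days on landiolol. The mean differences follow by weighting. For mortality 40% against 30% and a 25-day stay for those saved:

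- survivors: (60·15 + 10·25)/70 − 15 = 16.4 − 15 = +1.4 days
- non-survivors: 7 − (10·12 + 30·7)/40 = 7 − 8.25 = −1.25 days

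Simulation (4,000 trials per scenario, 100 per arm, two-sided 0.05 log-rank):

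| Mortality, control vs landiolol | Survivor test: landiolol longer | Mean difference (days) | Non-survivor test: landiolol shorter | Mean difference (days) |
|---|---|---|---|---|
| 40 vs 30%, 50 vs 40% | 9–17% | +1.4 to +2.5 | 13–15% | −1.0 to −1.2 |
| 50 vs 30%, 60 vs 40% | 24–43% | +2.9 to +5.0 | 27–30% | −1.7 to −2.0 |

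If those saved stay 15 days like other survivors, the survivor test is unbiased but the non-survivor test is still shifted (12–31% shorter).

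**All randomised patients.** In the scenarios of the table, a comparison of time to discharge alive, with deaths kept in the risk set as never discharged, favoured landiolol in 22–25% of trials for a 10-point mortality benefit and in 69–74% for a 20-point benefit. It pointed significantly the wrong way in at most 0.1%.

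**The case against.** The strongest reply is that little depends on this. The endpoints are secondary and the article bars confirmatory conclusions from them. Mortality is tested separately, so a reader would see a survival difference beside any stay result. That stands, and it keeps the point out of the first rank. It does not remove it: the article's caution concerns type I error from multiple testing and does not mention selection, which no multiplicity adjustment corrects.

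Second, the bias needs an effect on who survives, and under the moderate model it would hardly be noticed in a trial of this size. Both statements are right. The large error rates need large mortality benefits and long stays among the patients saved, and nothing in the documents supports those values over others. A reader might infer that the planned tests are likely to mislead seriously; the documents do not show that.

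Third, the opposite meaning of a short stay in the two subsets is a reason to show them apart. Agreed, for description. It does not justify between-arm tests within them.

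Fourth, the full analysis plan is not shown and might add a comparison in all randomised patients. It might, but the split is already fixed in both the endpoint table and the analysis text.

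A reader might also infer that the plan pools all patients and censors deaths in a Kaplan–Meier curve. The article does not say so, and if survivors are those discharged alive there are no deaths to censor. That approach matters only as a fallback to avoid. With an assumed discharge hazard of 0.06 per day in both arms and death hazards of 0.04 (control) and 0.02 (landiolol), it gives 1 − exp(−0.06·28) = 81% discharged by day 28 in both arms. The proportions actually discharged alive are 0.06/0.10·(1 − exp(−2.8)) = 56% and 0.06/0.08·(1 − exp(−2.24)) = 67%.

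**Conclusion.** The point holds as a flaw of principle in two secondary analyses. The planned tests of stay condition on a post-randomisation outcome and are biased if landiolol changes who survives. The size is nil with equal mortality and case mix, small under moderate selection, and substantial only under the stronger assumptions. The direction among non-survivors depends on the model: longer on landiolol under moderate selection, shorter under the three-type model. That is a further reason not to interpret a P value there. The primary conclusion, its alpha and the sample size of 200 are unaffected. Confidence is high on the principle and low on the magnitude, because the documents give no figures from which to fix it.

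**What to change.** Make the between-arm comparison of ICU stay and of hospital stay in all randomised patients. Use the cumulative incidence of discharge alive with death as a competing event, tested by Gray's test or a subdistribution hazard ratio, stratified by atrial fibrillation as in the randomisation. State the time horizon for each. Report stay in survivors and in non-survivors descriptively by arm, without P values, and do not replace the split by a pooled Kaplan–Meier analysis with deaths censored.

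ICU-free days to day 28, with death ranked worst, may be added as a supportive analysis. Its small downside is that it is partly driven by mortality, which is already an endpoint, and that it truncates long stays. The discharge-alive comparison also reflects mortality as well as speed of recovery, so it should be read beside the mortality results.

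The cost is a change of wording and standard software. Stay and survival status are already needed for the listed endpoints, and sample size, visits and treatment do not change.

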## Discussion

Despite intensive research, morbidity and mortality of patients with sepsis remain high [39]. Hence, novel therapeutic concepts are urgently needed. Recently, the use of beta-blockers during sepsis has been suggested [10, 28–30, 32, 41]. This represents a true innovation, as current guidelines recommend beta-mimetics [40]. The potential benefits of beta-blockers are most likely due to their pleotropic effects and include myocardial protection, modulation of inflammatory processes, and improvements in organ functions [3, 22, 42–44]. However, it is still unclear which patients would benefit most from this intervention.

Morelli et al. [10] (and later others [28–30, 32]) showed that a HR reduction in patients with septic shock, after adequate resuscitation with fluids, vasopressors, and inotropes, was not associated with an increase in AEs and did not trigger an increase in vasopressor support. As in the original protocol by Morelli et al. [10], the target HR in the present study is < 95 bpm, which is based on studies showing poorer patient outcomes when this threshold is exceeded and studies showing good tolerance after achieving this target with beta-blockers [7, 11, 45–48]. More recently, several studies conducted in China [28–30, 32] that selected a similar HR target showed good tolerance of the beta-blocker treatment. Therefore, the HR target of < 95 bpm seems appropriate for further comparison and optimal with respect to feasibility and tolerance.

In order to minimize the risk of hemodynamic compromise, patients are only included in the study after at least 24 h of adequate fluid resuscitation and vasopressor support. In addition, landiolol is started at a low dose of 1 mcg/kg/min (as supported by landiolol sepsis [49], postoperative [50], and heart failure studies [51]) and titration is performed conservatively at 20-min intervals (5 half-lives) [35]. The HR target should be reached within the first 24 h, as supported by published data [28–30, 32].

Esmolol is the beta-blocker that has been most frequently evaluated in patients with sepsis, as its pharmacokinetic profile allows for rapid titration when used intravenously [10, 27–29, 31]. However, landiolol has demonstrated a more favorable pharmacokinetic and pharmacodynamic profile than esmolol [52–55]. Landiolol has a faster onset (1 min vs 2 min) and shorter half-life (4 min vs 9 min) than esmolol, which should allow for more rapid titration and enhanced safety [35]. Furthermore, the beta1 selectivity of landiolol is eight times higher than that of esmolol, resulting in a beta1/beta2 ratio of 255 [35]. This provides landiolol with more profound negative chronotropic effects and a lesser degree of negative inotropic and hypotensive action [36–38, 56].

This study will investigate whether HR control using the short-acting beta-blocker landiolol is feasible, safe, and effective in patients with septic shock and persistent tachycardia, and provide a better understanding of the potential role of beta-blockers in this patient population.

## Trial status

Protocol version 3.0 dated 3 January 2018. The first participant was enrolled on 24 February 2018.

## Abbreviations

APACHE II: Acute Physiology and Chronic Health Evaluation II
AV: Atrioventricular
Bpm: Beats per minute
CI: Cardiac Index
CO: Cardiac output
ELWI: Extravascular lung water index
GEDI: Global end-diastolic volume index
HR: Heart rate
ICU: Intensive care unit
LVEF: Left ventricular ejection fraction
MPAP: Mean pulmonary arterial pressure
PAOP: Pulmonary arterial occlusion pressure
NYHA: New York Heart Association
PICCO: Pulse contour cardiac output
SOFA: Sequential Organ Failure Assessment
SPIRIT: Standard Protocol Items: Recommendations for Interventional Trials
TAPSE: Tricuspid annular plane systolic excursion
VTI: Velocity time integral
